#### Participants

This study aims to recruit 500 women with an abnormal annual Pap test and follow-up scheduling for colposcopy at EFHC or PAC. Based on the current patient flow in the two clinics, we expect to randomize approximately 100 women from EFHC and 400 from PAC. Entry criteria will include women of age 18 or older who speak either English or Spanish and who have received an annual Pap test that warrants scheduling for colposcopy at EFHC or PAC. Women scheduled for a repeated Pap test or repeated colposcopy as follow up to a previous abnormality will not be enrolled because they may already have completed their initial information seeking process.

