#### Intervention

As soon as the patient has received notification of the lab Pap test result and has been scheduled for a colposcopy appointment, the appropriate control or intervention letter from the provider will be sent, along with a letter informing the patient about the study. The Usual Care letter from the provider will confirm the abnormal Pap and remind the patient of the scheduled follow-up appointment for colposcopy. The Intervention (CIS + Questions) letter from the provider will convey the same appointment information as the Usual Care letter. It will, in addition, ask the patient or a designate to [contact]-CANCER and it will suggest some questions to ask about abnormal Pap tests and colposcopy. The suggested questions are: "What does an abnormal Pap test mean?", "What is colposcopy and what can I expect during colposcopy?", and "How will it benefit me to take the test?"

Consistent with the Institute of Medicine's [42] recommendation, the letters will be appropriate for reading skills at or below an eighth-grade level. The Lexile, a measure of reading difficulty, will be used to gauge reading level [43,44].

Letters will be written in the patient's primary language, Spanish or English. They will be mailed on PAC or EFHC letterhead with a signature per the patient's provider. Text will be typed double-spaced in large font, filling less than a page. Like all materials planned for use in the RCT, the proposed letters will be reviewed with community members and providers during the initial formative phase of the study. The final content of the Usual Care and Intervention letters will be based on input from patients and providers.

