#### CIS data collection

Once CIS's usual service is complete, the information specialist will ask the customer service questions in the order listed previously. ECRF will be programmed in such a way that a zip code which falls within the study area will trigger an electronic prompt for the information specialist to ask a series of probing questions. The goal of the probing questions will be to determine if the caller is a part of the study population and if so, from which clinic and which study group (Intervention versus Usual Care). The HFO code will be re-coded to a study code accordingly.

The first probing question is, "Have you or someone you know recently had an appointment at Prentice Ambulatory Clinic or Erie Family Health Center in Chicago? If yes, which clinic?" If the caller responds "no," then a non-study HFO code is used and no more probing questions are asked. If the caller responds either "yes, PAC" or "yes, Erie" the second probing question is asked.

The second probing question is, "Did you or someone you know recently receive a call or letter about having a colposcopy for a positive pap test?" If the answer is "no," then a non-study HFO code is used. If the caller answers, "yes," then the third probing question is asked.

The third probing question is, "Did your letter or telephone call ask you to call [name]?" If the answer is "no," then the call is coded as either PAC Usual Care or EFHS Usual Care, depending on the caller's answer to the first probing question. If the caller answers "yes," then the call is coded as either PAC Intervention or EFHS Intervention, depending on the caller's answer in the first probing question.

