#### Statistical analysis

Based on information provided by site providers, we estimate a final N of 500 (250 intervention, 250 control) consented for follow-up to be reasonable and achievable within the one-year recruitment window. The study has four specific aims:

**Aim 1 **is to conduct focus groups about the CIS, and the targeted study letter with 10 patients and 10 providers from two large clinics that serve low-income women in Chicago. Transcripts of the focus groups will be analyzed qualitatively for content to determine the totality of ideas that emerge from the discussions. All data will be summarized descriptively. In particular, information will be compiled on familiarity with and views about the CIS, barriers and facilitators to telephoning the CIS for information about cancer prevention and screening and perceived information support needs for following up abnormal Pap tests.

**Aim 2 **is to randomize and enroll all women between ages 18-60 who receive an abnormal annual Pap test with follow-up scheduling for colposcopy at two clinics for underserved women. Randomization to Usual Care or Intervention will be conducted using the previously described procedure.

**Aim 3 **is to compare the number of telephone calls made to the CIS by patients randomized to Intervention versus Usual Care in order to test the hypothesis that a targeted physician mailing that asks patients to call the CIS and suggests questions will increase CIS call volume compared to Usual Care control. The outcome measure will be whether or not a study participant calls the CIS. Proportions will be compared between study groups using the Cochran-Mantel-Haenszel chi-square test [50]. With 250 persons per group, there is 80% power to detect a difference of a 5% call rate in the control group versus a 12% call rate in the intervention group. There is greater than 99% power to detect the anticipated difference of 5% in the control group versus 40% in the intervention group.

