To compare patient satisfaction between the two groups, the four-item CAHPS scale will be used where each item is coded 1 (never, sometimes), 2 (usually) or 3 (always). The sum of these four items will have a range of 4-12. If this range represents 4 standard deviation units, then a conservatively large estimate of the standard deviation is 2 units on the CAHPS 4-item scale. Anticipated sample size for the analysis of satisfaction data (given expected follow-up rates of 55% control and 75% intervention) is 293 (control N = 124, intervention N = 169). These sample sizes have 80% power to detect an effect size of 0.34, where effect size is defined as the mean difference between intervention and control, divided by the standard deviation. With an estimated standard deviation of 2, this effect size translates into a mean difference of 0.68 (.34 × 2). With these assumptions for the sample size, the study is powered to detect a consistent difference between the groups of one response category for one item. Before the satisfaction data are analyzed, participant characteristics will be compared between the control and intervention subsamples to determine any selection bias that may have occurred due to differential follow-up between the groups. Satisfaction data will then be analyzed using a two-factor analysis of variance, with clinic (EFHC versus PAC) as one between-subjects factor and study condition (Usual Care versus Intervention) as the other. The interaction term will determine whether the intervention effect is different between the two clinics. Any demographic characteristics found to be different between the groups will be included in this analysis as covariates. Other potential covariates are whether the physician is patient's usual provider, language barrier, availability of needed translation, and whether family members accompany the patient to the appointment. The intervention by ethnicity (Hispanic vs. African American) interaction will also be tested: prior studies neither support nor negate such interaction. For all power calculations, a two-tailed test and a Type I error rate of 5% is assumed.

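### Among callers who pass the screening probes, Usual Care is the residual code, so calls from excluded patients and Intervention designates can enter the control count of a primary outcome

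*Protocol article*

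**What the plan says.** Calls to the CIS are one of three primary outcomes. The section on telephone calls to the CIS allocates four study codes, one for each combination of clinic and arm. It also says that the call records are de-identified and cannot be linked to a patient's other data.

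The CIS data collection section fixes the coding sequence:

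- **Trigger:** "a zip code which falls within the study area will trigger an electronic prompt".
- **Probe 1:** a recent appointment at one of the two clinics, for the caller or someone the caller knows. 'No' gives a non-study code.
- **Probe 2:** a recent call or letter about colposcopy for a positive Pap test, again for the caller or someone the caller knows. 'No' gives a non-study code.
- **Probe 3:** whether the caller's own letter or telephone call asked her to call the service. 'Yes' gives Intervention. On 'no', "then the call is coded as either PAC Usual Care or EFHS Usual Care".

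Two other sections bear on this. Participants (experimental phase) states: "Women scheduled for a repeated Pap test or repeated colposcopy as follow up to a previous abnormality will not be enrolled". Intervention says of the Intervention letter: "It will, in addition, ask the patient or a designate to" telephone the service. Only that letter invites a designate.

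Statistical analysis (Aim 3) defines the outcome as whether a participant calls and compares proportions between the randomised groups.

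**The concern.** The probes are meant to establish whether a caller belongs to the study population and, if so, to which arm. They do neither fully. None asks whether the colposcopy is a first or a repeat, and none offers a way to record that the arm is unknown. Usual Care therefore receives whatever is left over.

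The third probe also changes its reference. The first two cover the caller or someone the caller knows, while the third covers only the caller's own letter or call. Designates, whom the Intervention letter invites, are exactly the callers who received no letter themselves.

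At stake is the numerator of a primary outcome. It can contain calls that do not belong to the randomised denominator, or that belong to the other arm. Because calls are anonymous, such errors cannot be found or corrected afterwards.

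**Working it through.** **Step 1. Follow the rule for each kind of caller who passes the ZIP trigger.**

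| Caller | Probes 1 and 2 | Probe 3 | Code | Effect on contrast |
|---|---|---|---|---|
| Usual Care patient, correct answers | yes | no | Usual Care | none |
| Repeat-colposcopy patient contacted by the clinic | can be yes | no | Usual Care | shrinks |
| Intervention designate reading probe 3 literally | yes | no | Usual Care | shrinks |
| Intervention designate answering for the patient | yes | yes | Intervention | none |
| Intervention patient who does not recall the request | yes | no | Usual Care | shrinks |
| Usual Care or non-randomised caller wrongly saying yes | yes | yes | Intervention | widens |
| Patient and her designate both calling | yes | yes | Intervention, counted twice | widens |

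**Step 2. Reproduce the plan's power.** The inputs are in Statistical analysis. "With 250 persons per group, there is 80% power to detect a difference" is stated for a "5% call rate in the control group versus a 12% call rate in the intervention group", and "a two-tailed test and a Type I error rate of 5% is assumed". With n = 250 per group and p̄ the mean of the two rates:

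power = Φ{ [(p2 − p1) − 1.96·√(2p̄(1 − p̄)/n)] / √[(p1(1 − p1) + p2(1 − p2))/n] }

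For 5% versus 12%, p̄ = 0.085. The null term is 1.96 × 0.02494 = 0.0489 and the denominator is 0.02475. Power = Φ[(0.07 − 0.0489)/0.02475] = 0.803, so the stated 80% is reproduced. For the "anticipated difference of 5% in the control group versus 40% in the intervention group", power exceeds 0.999, again as stated.

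**Step 3. Illustrate the two shrinking routes.** Let m be the share of Intervention calls coded Usual Care and k the number of non-randomised calls coded Usual Care. Neither is in the article; **both are assumptions**.

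- observed control rate = 0.05 + m·p2 + k/250
- observed Intervention rate = p2·(1 − m)

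One stray call moves the difference by 1/250 = 0.4 points. One call moved between arms changes it by 0.8 points. At 5% versus 12% there are only 12.5 and 30 calls.

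| True rates | m | k | Observed | Difference (points) | Power |
|---|---|---|---|---|---|
| 5% vs 12% | 0 | 0 | 5.0% vs 12.0% | 7.0 | 80% |
| 5% vs 12% | 5% | 0 | 5.6% vs 11.4% | 5.8 | 64% |
| 5% vs 12% | 10% (3 calls) | 0 | 6.2% vs 10.8% | 4.6 | 45% |
| 5% vs 12% | 0 | 5 | 7.0% vs 12.0% | 5.0 | 48% |
| 5% vs 12% | 10% | 5 | 8.2% vs 10.8% | 2.6 | 17% |
| 5% vs 40% | 0 | 0 | 5.0% vs 40.0% | 35.0 | >99% |
| 5% vs 40% | 10% (10 calls) | 5 | 11.0% vs 36.0% | 25.0 | >99% |
| 5% vs 40% | 20% | 20 | 21.0% vs 32.0% | 11.0 | 80% |
| 5% vs 40% | 30% | 10 | 21.0% vs 28.0% | 7.0 | 44% |

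The two widening routes in Step 1 are not in these formulas. The table shows sensitivity to the shrinking routes only and is not an estimate of net bias.

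**The case against.** **The filters come first.** A reader might infer that every clinic caller who was not asked to call ends up in Usual Care. The article does not support that: the ZIP trigger and two probes precede the arm question, and failing any of them keeps the call out of the study codes. This stands, and the point is confined to callers who pass them.

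**Designates are not miscoded by rule.** One who is calling because of the patient's letter may well answer 'yes'. Patients who call because of the letter are also unlikely to forget its request. Both are fair. The defect is that a literal and truthful answer by a designate gives the wrong code.

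**The direction is not certain.** A reader might infer a guaranteed bias toward no difference. False 'yes' answers and more than one call per patient would widen the contrast, and only the Intervention letter invites a second caller. This also stands.

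**The error rates are invented.** At the protocol's 5% control call rate, five stray callers would imply about 5/0.05 = 100 contacted non-randomised women, and the article gives no such number. At the anticipated effect, moderate errors leave power intact. Both are correct.

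**There is a second measure.** The exit interview asks identified participants about their own calls and calls made on their behalf, so arm is known. But it reaches only women who attend and consent, and attendance is itself expected to be 55% versus 75%. The Discussion says that neither source can verify the other. It mitigates the problem without removing it.

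**Conclusion.** The concern holds in a limited form. Followed exactly, the coding rule can place calls from excluded patients and from Intervention designates in the control count of a primary outcome, with no code for doubt and no later means of correction. These two routes shrink the contrast. The net size and direction across all routes cannot be derived from the article.

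Under the assumed rates, the comparison is fragile at 5% versus 12%: three miscoded calls or five stray ones bring power to 45% or 48%. At 5% versus 40%, the same errors together leave power above 99% and cost 10 points of the estimated difference. A reader might infer that the stated power is wrong. It is not: it reproduces, and it simply assumes error-free coding.

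The rule should be changed before letters are mailed, because the repairs are cheap then and unavailable later.

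**What to change.** 1. Reword the third probe to ask about 'your letter or call, or that of the person you are calling for'.
2. Add a probe on whether this is a first or a repeat colposcopy, and give repeats a non-study code.
3. Allocate two of the blank How Found Out codes to 'PAC, arm not confirmed' and 'EFHC, arm not confirmed', for callers who cannot say.
4. Report the call comparison with unconfirmed calls placed in Usual Care and, as a sensitivity analysis, with them excluded.

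A code printed on the letters should not become a condition for counting a call in the primary comparison. Usual Care women have no instruction to call and less reason to have the letter at hand, so the code may be missing more often in that arm. Dropping those calls would lower the control rate and inflate the effect.

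The cost is a slightly longer call script, in a service where practice takes priority over research, and a few unclassified calls. These changes do not remove false 'yes' answers or multiple calls per patient, which the report should acknowledge.

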### Statistical analysis plan

#### Quality control and data management

Data management and quality control will be the joint responsibilities of the study coordinator and the laboratory data manager, utilizing the resources of the Biostatistics Core Facility of the Robert H. Lurie Comprehensive Cancer Center. Study databases in Excel and SPSS will be developed to house all study data. Databases, stored on the local PCs of the data manager and study coordinator, will be encrypted and password protected. Entered data will be monitored and questionable values will be checked and corrected as appropriate. Randomization balance will be evaluated quarterly to assure equal sample sizes in the study groups.

#### Statistical analysis

Based on information provided by site providers, we estimate a final N of 500 (250 intervention, 250 control) consented for follow-up to be reasonable and achievable within the one-year recruitment window. The study has four specific aims:

**Aim 1 **is to conduct focus groups about the CIS, and the targeted study letter with 10 patients and 10 providers from two large clinics that serve low-income women in Chicago. Transcripts of the focus groups will be analyzed qualitatively for content to determine the totality of ideas that emerge from the discussions. All data will be summarized descriptively. In particular, information will be compiled on familiarity with and views about the CIS, barriers and facilitators to telephoning the CIS for information about cancer prevention and screening and perceived information support needs for following up abnormal Pap tests.

**Aim 2 **is to randomize and enroll all women between ages 18-60 who receive an abnormal annual Pap test with follow-up scheduling for colposcopy at two clinics for underserved women. Randomization to Usual Care or Intervention will be conducted using the previously described procedure.

**Aim 3 **is to compare the number of telephone calls made to the CIS by patients randomized to Intervention versus Usual Care in order to test the hypothesis that a targeted physician mailing that asks patients to call the CIS and suggests questions will increase CIS call volume compared to Usual Care control. The outcome measure will be whether or not a study participant calls the CIS. Proportions will be compared between study groups using the Cochran-Mantel-Haenszel chi-square test [50]. With 250 persons per group, there is 80% power to detect a difference of a 5% call rate in the control group versus a 12% call rate in the intervention group. There is greater than 99% power to detect the anticipated difference of 5% in the control group versus 40% in the intervention group.

**Aim 4 **is to compare the Intervention and Usual Care groups' medical follow-up in the 6 months after abnormal Pap test notification and exit interview data at Pap test follow-up. The two outcome measures will be the dichotomous variable of timely follow-up completion (yes, no) as well as the CAHPS satisfaction questionnaire. The proportion of participants completing follow-up within 6 months will be compared between study groups using the Cochran-Mantel-Haenszel chi-square test. It is anticipated that 450 participants will consent to participation. With 225 persons per group, there is 80% power to detect a difference between a 55% appropriate follow-up rate in the control group versus a 68% rate in the intervention group. There is 99% power to detect the anticipated difference of 55% in the control group versus 75% in the intervention group.

To compare patient satisfaction between the two groups, the four-item CAHPS scale will be used where each item is coded 1 (never, sometimes), 2 (usually) or 3 (always). The sum of these four items will have a range of 4-12. If this range represents 4 standard deviation units, then a conservatively large estimate of the standard deviation is 2 units on the CAHPS 4-item scale. Anticipated sample size for the analysis of satisfaction data (given expected follow-up rates of 55% control and 75% intervention) is 293 (control N = 124, intervention N = 169). These sample sizes have 80% power to detect an effect size of 0.34, where effect size is defined as the mean difference between intervention and control, divided by the standard deviation. With an estimated standard deviation of 2, this effect size translates into a mean difference of 0.68 (.34 × 2). With these assumptions for the sample size, the study is powered to detect a consistent difference between the groups of one response category for one item. Before the satisfaction data are analyzed, participant characteristics will be compared between the control and intervention subsamples to determine any selection bias that may have occurred due to differential follow-up between the groups. Satisfaction data will then be analyzed using a two-factor analysis of variance, with clinic (EFHC versus PAC) as one between-subjects factor and study condition (Usual Care versus Intervention) as the other. The interaction term will determine whether the intervention effect is different between the two clinics. Any demographic characteristics found to be different between the groups will be included in this analysis as covariates. Other potential covariates are whether the physician is patient's usual provider, language barrier, availability of needed translation, and whether family members accompany the patient to the appointment. The intervention by ethnicity (Hispanic vs. African American) interaction will also be tested: prior studies neither support nor negate such interaction. For all power calculations, a two-tailed test and a Type I error rate of 5% is assumed.

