#### Randomization

Patients will be randomized to two conditions that involve different letters from the provider. *Usual Care *participants will receive a generic letter reminding them of their follow-up appointment. *Intervention *participants will receive a targeted letter reminding them of the follow-up appointment, asking them or someone they designate to call CIS, and suggesting some questions to ask.

The patient will be the unit of randomization and the project statistician will prepare and manage the randomization scheme. Separate randomizations will be performed for EFHC and for PAC. Usual Care and Intervention letters will be placed in envelopes. At the time randomization envelopes are selected, group allocation will be concealed from study staff and clinic staff so that there is no selection bias in the randomization process.

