#### Outcomes and measures

##### Primary outcomes

There are three primary study outcomes 1) telephone calls to CIS (call volume); 2) timely completion of medical follow-up (within 6 months); 3) patient satisfaction with doctor-patient communication at medical follow-up.

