##### Telephone calls to the CIS

The CIS will tabulate calls originating from the study. When CIS information specialists answer the telephone, they log call and caller information into a standard Electronic Call Record Form (ECRF). With the caller's consent, three customer service questions are asked of all callers:

1. Have you used our service before?

2. How did you find our number to call?

3. What is your home ZIP code?

The ECRF response field for Question #2, "How Found Out" (HFO) has many codes, e.g., 300 - TV, 400 - radio, 801- ACS etc., including blank codes that can be assigned to a specific promotion or research study. Four How Found Out response codes will be allocated to identify the conditions in this study: Code 1: PAC, Usual Care; Code 2: PAC, Intervention; Code 3: EFHC, Usual Care; Code 4: EFHC, Intervention.

Information specialists will follow a series of steps (see: ECRF programming below) to determine which, if any, of the four codes should be assigned to a call.

Operationalizing call tracking in this way produces de-identified data. Consequently, it will not be possible to link ECRF-coded call data to the patient's other individual level outcome data. To accomplish such linking, self-reported data on calls to CIS also will be collected from identified participants during the exit interview. This will allow exploratory examination of whether calling the CIS appears to mediate more timely follow-up and improved provider-patient interaction.

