CIS is also favorably positioned to partner in the complex endeavor of research. Although it is first and foremost a service organization, CIS has its own research program complete with a research agenda dedicated to bridging the gap between research and service [4]. CIS staff is trained to conduct research studies embedded in the service environment. From the perspective of CIS, this study is a model of collaboration. The research engages CIS with academic researchers and public health clinics in a mutually beneficial collaboration that strives to produce health benefits for the underserved.

While the study has considerable strengths, it also has limitations. First, in the clinics and within the CIS, practice/service takes priority over research. Therefore, extra effort will be required to integrate research into daily practice and service activities in a manner that ensures correct implementation of data collection processes. Second, a primary outcome, calls to the CIS, will be measured via patient self-report as well as via calls recorded by CIS as coming from the study. Because CIS calls are anonymous, call information cannot be used to verify self-report or vice versa.

These limitations notwithstanding, the present study has the potential to connect the CIS to low-income patients who need cancer screening information. By doing so, the study may contribute to overcoming communication barriers that underlie cancer health disparities.

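### Primary outcome 1 is both a call count and a yes/no per woman, and neither planned data source gives the yes/no for 250 women per group

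*Protocol article*

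**What the plan says.** **Definition.** The Primary outcomes section describes the first outcome as call volume. In the Statistical analysis section, Aim 3 sets out to "compare the number of telephone calls made to the CIS by patients randomized to Intervention versus Usual Care", and its hypothesis concerns call volume. The same paragraph then says "The outcome measure will be whether or not a study participant calls the CIS", followed by "Proportions will be compared between study groups using the Cochran-Mantel-Haenszel chi-square test". Power is given for 250 persons per group: 80% for 5% versus 12%, and above 99% for the anticipated 5% versus 40%.

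**CIS records.** The section on telephone calls says "The CIS will tabulate calls originating from the study". Each call receives one of four codes (clinic by arm) through probing questions that accept a caller asking for herself or for someone she knows. The section adds: "Consequently, it will not be possible to link ECRF-coded call data to the patient's other individual level outcome data".

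**Self-report.** Women are asked at the exit interview whether and how often they called, and whether others called for them. The interview follows written consent taken at the colposcopy visit. The telephone-calls section gives these data an exploratory linking role, but the Discussion says that "a primary outcome, calls to the CIS, will be measured via patient self-report as well as via calls recorded by CIS".

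**Who may call.** The Intervention letter is described as "asking them or someone they designate to call CIS". The Usual Care letter contains no such request.

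**The concern.** A count of calls and a yes/no per woman are different outcomes and need different analyses. The article fixes the outcome, the test and the denominator in one paragraph, so the conflict is in what is stated and is not a matter of detail left to a fuller document.

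Two things are at stake. First, the stated analysis cannot be carried out as written on either source. Second, the obvious workaround is to enter CIS calls as if they were women. The Cochran-Mantel-Haenszel test would then treat as independent some calls that came from, or were made for, the same woman. The exit-interview questions show that the protocol expects repeat calls and calls by others.

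**Working it through.** **1. The plan's power figure.** Inputs from Aim 3: 250 per group, 5% versus 12%, two-sided 5%. The pooled proportion is 0.085.
- SE under no difference: √(2 × 0.085 × 0.915 / 250) = 0.02494.
- SE under the alternative: √((0.05 × 0.95 + 0.12 × 0.88) / 250) = 0.02475.
- Power: Φ((0.07 − 1.96 × 0.02494) / 0.02475) = Φ(0.853) = 80.3%.

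The stated 80% reproduces, provided each of the 250 women per group is classified once as caller or non-caller.

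**2. Can CIS records supply that classification?** No. They hold calls with a clinic-by-arm code, and the article gives no rule or identifier that reduces calls to distinct women.

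**3. Can self-report?** Only for women interviewed. The protocol expects 450 to consent (225 per group) and follow-up of 55% and 75%: 225 × 0.55 ≈ 124 and 225 × 0.75 ≈ 169. The pooled proportion is (124 × 0.05 + 169 × 0.12) / 293 = 0.0904.
- SE under no difference: √(0.0904 × 0.9096 × (1/124 + 1/169)) = 0.0339.
- SE under the alternative: √(0.0475/124 + 0.1056/169) = 0.0317.
- Power: Φ((0.07 − 1.96 × 0.0339) / 0.0317) = Φ(0.11) ≈ 54%.

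For 5% versus 40% power stays above 99%. Attendance is the second primary outcome, so this subset is formed after randomisation by something the letter is meant to change.

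**4. What if CIS calls are divided by 250 and tested as a proportion?** Let a share p of women call in both arms (no true difference), and let a fraction q of callers generate one extra call. The value of q is an assumption. Per woman, the mean number of calls is p(1+q) and the variance is p(1+3q) − p²(1+q)². The test assumes p(1+q)[1 − p(1+q)].

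Example, p = 0.05 and q = 0.20 in both arms: mean 0.06; true variance 0.05 × 1.6 − 0.0036 = 0.0764; assumed variance 0.06 × 0.94 = 0.0564; ratio 1.355. The effective critical value is 1.96/√1.355 = 1.684, so the true two-sided error is 9.2%.

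Simulating the clinic-stratified test (50 + 200 women per arm, at least 200,000 trials per setting, no continuity correction) gives:

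| Callers with one extra call | p = 5% | p = 12% |
|---|---|---|
| none | 4.9% | 4.9% |
| 10%, both arms | 7.0% | 7.6% |
| 20%, both arms | 9.2% | 9.7% |
| 30%, both arms | 10.7% | 11.6% |
| 10%, Intervention only | 6.6% | 8.1% |
| 20%, Intervention only | 9.7% | 14.7% |
| 30%, Intervention only | 13.8% | 24.0% |

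Counting each calling woman once gives 4.8-5.1% throughout.

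**The case against.** **The workaround is not in the document.** A reader might infer that the trial will divide calls by 250. Aim 3 names no data source, and the Discussion lists self-report beside CIS records, so the documents do not support that as a statement of what will happen. Aim 3 can also be read as self-report, since the Statistical analysis section describes its 500 women as consented for follow-up. That reading meets the difficulty in step 3 and conflicts with the 450 expected to consent and the 124 and 169 expected for satisfaction data. The inflation is therefore conditional; the mismatch between outcome and data is not.

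**No duplication rate is given.** This stands. The range begins at no inflation.

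**Designate calls need not be duplicates.** A reader might infer that every designate call adds a spurious woman to the Intervention arm. The letter offers the designate as an alternative caller. One who calls instead of the patient adds one call for one woman; only a call in addition to another for the same woman does harm.

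**Extra calls may be a real effect.** If the outcome is call volume, additional calls prompted by the letter are part of what is being measured. The Intervention-only rows are type I error only under the per-woman definition. The 12% column also assumes 12% calling in both arms, whereas the protocol expects 5% in control.

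**The anticipated effect is large and the limitation is disclosed.** At 5% versus 40%, power is not in question. The reported share of women reached still could be: with 20% extra calls, 40% would appear as 0.40 × 1.2 = 48%. The article discloses that CIS calls are anonymous and cannot be linked to individual data, but it does not adapt the Aim 3 outcome or test to that.

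**Conclusion.** The point holds as an inconsistency in a primary outcome. It is given two definitions, and the one that is tested cannot be obtained for 250 women per group from either source. CIS records lack the woman as a unit. Self-report covers a selected subset of about 293, with about 54% power for 5% versus 12%.

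Inflation of the type I error follows only if calls are entered as women. Its size then depends on assumed duplication: with equal rates in both arms, from 5% at none to 11-12% when 30% of callers generate an extra call. With extra calls in the Intervention arm only, at 10-30%, it is about 7-14% at a 5% caller rate and 8-24% at 12%, under the per-woman definition. It would be wrong to report the trial's error rate as known to be inflated.

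**What to change.** Choose one definition and one decisive data source, and use them consistently in Primary outcomes, Aim 3 and the power statement.

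**(a) Keep the per-woman outcome.** Define it as at least one CIS call by the woman or a designate, over all randomised women, by clinic and arm. Print a non-identifying code on both letters, have the specialist record it at the existing probing step, and collapse calls to one per letter. State how calls without a code are handled, for example by bounding: all counted as new women, or none. Cost: one call-record field, one printed code and ethics review, since calls would become traceable to a letter before consent. Some callers will not have the letter to hand.

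**(b) Keep call volume.** Analyse calls per randomised woman by arm and clinic as a rate allowing for over-dispersion, do not describe it as a proportion of women, and drop or restate the 80% power. The CIS data are four totals, so a model with clinic and arm leaves one degree of freedom (4 − 3) and cannot estimate over-dispersion usefully. The factor should be set in advance over a range. Under the model above, relative to Poisson, it is (1+3q)/(1+q): 1.18, 1.33 and 1.46 at q = 10%, 20% and 30%. Cost: analysis wording only.

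Under either option, label exit-interview self-report as supportive. Do not use the question on previous use of the service to remove duplicates: it would drop women who used CIS before the study and would still count a woman and her first-time designate twice.
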